**Methods/design:**

This 2-year study is a theory-driven, multi-site, non-randomized study design with a cross-case analysis of 13 workplaces across four provinces in Canada. The first phase of the study includes the development of workplace-specific programs with the support of the intensive engagement of knowledge brokers. There will be a three-points-in-time evaluation with process and impact components involving the occupational health and safety (OHS) director, management, and workers with the goal of measuring changes in workplace policies, procedures, and practices. It will use mixed methods involving semi-structured key informant interviews, focus groups, surveys, site observations, and UV dosimetry assessment. Using the findings from phase I, in phase 2, a web-based, interactive, intervention planning tool for workplaces will be developed, as will the intensive engagement of intermediaries such as industry decision-makers to link to policymakers about the importance of heat and sun safety for outdoor workers.

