#### Sampling and recruitment of workplaces

The study is focusing on workers employed with utilities such as electrical distribution companies and those employed with medium-to-large municipalities and provincial wilderness parks. The initial criterion will be whether the organization has (at least) 20–100 employees engaged in outside work. Such outside work will be primarily of a brush-clearing, grounds-keeping, or landscaping nature (i.e., employees undertaking outdoor work on “soft” surfaces). It is anticipated that many utilities will have employees engaged in clearing vegetation from right-of-ways and trimming trees and shrubs near power lines. Municipalities will have employees maintaining municipal properties such as parks and will be engaged in grounds-keeping, lawn-mowing, and landscaping. It is anticipated that some organizations will contract out such brush-clearing or landscaping work and so will not be suitable participants. It is also anticipated that most OHS professionals will have to gain the support or permission of others in the organization in order to participate.

Workplaces were recruited through convenience sampling by using existing contacts of project partners and supporters. A number of the supporters who wrote letters of support for the project are workplaces who are interested in participating in the project; these were contacted through local and regional contacts of the partners on the project. Other potential participants were selected using a database of approximately 10,000 OHS professionals; individuals who occupy the position of OHS “manager,” “coordinator,” “advisor,” “lead”, and so on (there is great diversity of job titles for the individuals who oversee an organization’s OHS efforts). Initial contact was made with the OHS professional employed by a municipality, wilderness park, or utility by senior partners on the study to determine the personal interest of the OHS professional in the aims of the project and to ascertain the numbers and nature of work of the outside workers.

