**Fig. 10 Fig10:**
[figure not shown]
Sun Safety at Work sun safety advisor training meeting

The Sun Safety Advisors will interact with one to four workplaces each depending upon geographical convenience. To initiate their relationship with the workplaces, they will meet with their worksites together with the project partner who made the initial contact to reassure the workplace of the level of support offered by the project team. They will engage with the participating worksites (including regular face-to-face contact) with management and workers, and will identify an internal “workplace champion” with whom to work closely. The workplace champion will be the workplace liaison and local project sponsor. The importance of the champion role has also been well explored as a means to ensure sustainability [80]. In previous projects of this type, the workplace occupational health and safety professional has often fulfilled this “workplace champion” role because of their involvement in occupational health and safety projects.

The project officers will collect the evaluation data at base-line before and after the first summer. This includes worker surveys and a face-to-face interview with the health and safety champion and managers. The interview information will focus on assessing the workplace’s organizational readiness for change; the worker surveys will evaluate workers’ awareness and knowledge of heat and sun protective behavior and practices, and when compared with the second evaluation, we will have metrics of change due to the intervention.

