#### The Sun Safety at Work implementation

The Sun Safety Advisors will help the companies develop their programs and policies (Sun Safety Action Plans), based upon the findings of the base-line surveys and interviews. The action plan will be tailored to suit each workplace and will be embedded within the companies’ occupational health and safety risk assessment and control framework and risk management systems. It will describe the evaluation process of the project and will specify proposed sun safety activities, the timeline for implementation, who is responsible, and how these activities fit into the legal obligation to create a safe workplace. The action plan will be for 3 years and will extend beyond the project’s funding and direct involvement to ensure sustainability of the initiatives in the workplaces.

The action plan will take into account the financial and organization capacity of the workplace to implement the activities, and depending upon where a workplace is on their sun safety “journey,” will include a phased approach to the implementation of the selected activities. The ability of the workplace to sustain their sun safety program (after the study is over) and their overall stated level of change commitment and sense of efficacy will be a key determinant for the selection of activities and the development of the action plan.

During the first summer, the Sun Safety Advisors will lead the educational initiatives by delivering toolbox talks, showing videos, attending and contributing to joint occupational health and safety committees, giving health and safety meeting presentations regarding sun safety topics, promoting and exhibiting sun safe behavior including the wearing of appropriate PPE, and generally providing current and accurate educational advice to be disseminated to the workforce. They will also advise on how best to implement programs and sun safety change initiatives the employer chooses to undertake and help implement any of the initiatives from a suite of resources proposed by the study.

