#### Phase 1: data collection and analysis

The evaluation will employ a multiple case study approach [81], with the participating workplaces as the units of analysis. The evaluation of the cases will be guided by the conceptual framework for knowledge transfer, dissemination, and utilization for sun safety in outdoor workplaces (Fig. 1) to capture changes in programs, policies, and procedures. Workplace evaluations will occur at three points in time. The baseline assessment will focus on understanding the unique characteristics of each workplace, their occupational health and safety management system, and their current sun safety policy and practices. The second evaluation will be conducted after the first summer (mid-point of the study). The third workplace evaluation will be conducted 18 months after the study’s start date. Finally, a cross-case evaluation matrix will be used to determine generalizable patterns and themes.

Data collection will use mixed methods involving multiple sources of information including semi-structured key informant interviews and focus groups with workers, management, and the occupational health and safety specialist to determine the current occupational health and safety policies and procedure, readiness to change, organizational culture, and barriers/facilitators to sun safety programming (for example, see Fig. 11 information and consent form). The focus groups with employees will explore barriers and facilitators from the perspective of the different workplace parties—workers, supervisors, managers, and occupational health and safety specialists—and a survey will address individual knowledge, attitudes, and behaviors toward sun safety in the workplace. Site observations will record the use of sun safety practices, and a UV dosimetry assessment will measure UV exposure of the employees in the second summer of engagement.

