**Fig. 11 Fig11:**
[figure not shown]
Sun Safety at Work consent form for interview with occupational health and safety lead

The data collection at baseline and mid-point will be conducted by the Sun Safety Advisors. The data collection at the final time point will occur by an independent researcher. This approach is being undertaken because the involvement of the Sun Safety Advisors in the baseline and mid-point evaluations is considered to be part of their relationship-building and knowledge translation activities with the workplaces.

The conceptual framework (Fig. 1) will guide the interpretation and analysis of the qualitative findings for each of the cases. The qualitative data will be coded and organized by the dimensions of the conceptual framework, including the details of the workplace context, the characteristics of the knowledge transfer intervention, the knowledge exchange, and the workplace’s knowledge utilization, including indicators of conceptual use, effort to use, procedural use, and structural use. Short-term and medium-term outcomes will be noted. Key issues and emergent themes will be identified. The quantitative data (surveys) will be analyzed with SPSS or SAS and will allow for comparisons across the three points in time and allow for cross-case comparisons.

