## Summary

Skin cancer represents a significant public health issue for Canada, with heat-stress recognized as an important emerging issue. For both conditions, occupational sun exposure is a significant risk factor. Sun Safety at Work Canada is a unique study in that it aims to develop a nationally applicable, effective, and sustainable sun safety program for outdoor workers that will address both skin cancer and heat illness prevention and can be implemented by individual workplaces and embedded into their existing occupational health and safety systems. This uncontrolled before-after cross-case comparison design does have its limitations in comparison to more rigorous designs, but it is a reasonable response to the realities of real-world research in workplaces where there is no social, legal, or economic imperative to adopt best practices or incorporate evidence-based research. Our expectations remain that the evaluation will provide a detailed understanding of the process of implementing workplace health interventions of evidence-based best practices. The dissemination of the findings will be guided by a comprehensive knowledge translation strategy that will allow for wide distribution of the project’s learnings as a way of influencing policy and practice. Part of this knowledge translation strategy is the use of conceptual frameworks of knowledge transfer to guide workplace interventions and research activities. This model of research, policy, and practice integration, in addition to the theoretically grounded, evidence-based, consultative approach to implementation science is respectfully offered to the research community as a model for workplace intervention research.

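### The article calls the change in worker surveys across the first summer an effect of the intervention, but its uncontrolled before-after design identifies only total change

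*Protocol article*

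**What the plan says.** The causal statement is in the Protocol article under Recruitment of Sun Safety Advisors. That section describes worker surveys on awareness and knowledge of heat- and sun-protective behavior and practices. It ends by saying that "when compared with the second evaluation, we will have metrics of change due to the intervention". On timing, the same section says: "The project officers will collect the evaluation data at base-line before and after the first summer". Phase 1: data collection and analysis confirms that the second evaluation follows the first summer, at the study's mid-point.

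Other parts of the article describe the design behind this contrast:

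- The abstract calls it a "multi-site, non-randomized study design with a cross-case analysis of 13 workplaces across four provinces in Canada". No comparison workplaces are described anywhere.
- The Summary concedes: "This uncontrolled before-after cross-case comparison design does have its limitations in comparison to more rigorous designs".
- Phase 1: data collection and analysis states: "The data collection at baseline and mid-point will be conducted by the Sun Safety Advisors". An independent researcher takes over only for the final evaluation.
- The Sun Safety at Work implementation says what happens between the two waves: "During the first summer, the Sun Safety Advisors will lead the educational initiatives by delivering toolbox talks", along with other educational work by the same advisors.

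**The concern.** The phrase about change due to the intervention is an unqualified causal claim about one contrast, baseline against the second evaluation. A before-after difference equals an intervention effect only if nothing else would have moved the outcome over the interval, or if a comparator shows how far it would have moved. The article provides no comparator. The interval is also one in which other movement is plausible, because the outcome is awareness and practice on sun and heat and the interval is a summer.

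At stake is what the study may conclude from its worker surveys. If the sentence carries through to reporting, all of the observed change will be presented as the program's achievement.

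**Working it through.** The article states no figure for this contrast: no survey size, effect size or error rate. There is nothing to reproduce, and the check is one of identification.

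**Step 1. What the contrast contains.** Write D for the second-wave survey result minus the baseline result. Then

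D = P + S + T + R + A

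- P: effect of the program.
- S: season. The waves fall before and after a summer, and workers may think and act differently about sun and heat once they have worked through one.
- T: secular trend. Under Sampling and recruitment of workplaces, sites came by convenience through existing contacts, and some had already written in support of the project. Such sites may have been changing anyway.
- R: repeat surveying. Workers asked about sun safety at baseline may answer or behave differently because they were asked.
- A: change in how workers answer the advisors. By the second wave, the person collecting the survey has spent the summer teaching its content and modeling the behavior it asks about. The article itself treats advisor data collection at these two waves as part of relationship-building and knowledge translation.

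**Step 2. What can be solved for.** Two waves, with every workplace treated, give one equation in five unknowns. P = D with the other terms summing to zero fits the data exactly. So does P = 0 with S + T + R + A = D. The data cannot choose between them. D identifies the sum, which is total change over the first summer.

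**Step 3. Whether another planned element supplies the missing information.**

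- *Cross-case analysis.* For workplaces j and k, subtracting one change from the other removes a shift common to both and leaves P(j) − P(k), plus any difference in their background terms. At best this shows that the program did more in one place than in another. It does not give the level of P at either. The compared features, such as intensity of advisor contact or investment in protective equipment, were chosen by the workplaces, so background differences need not cancel.
- *Third evaluation.* It is outside the contrast that the sentence describes. It changes the data collector and adds no untreated group.
- *UV dosimetry.* It is planned for the second summer only, so it has no baseline value.
- *Survey analysis.* The text describes comparisons across the three time points and across cases. Neither isolates P.

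**Step 4. Whether the Summary already corrects the sentence.** The Summary says that the design has limitations against more rigorous ones. It does not say that attribution is among them, and it does not refer to the survey contrast. The two statements stand in tension: one describes an uncontrolled design, the other claims a result that needs a control.

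**The case against.** The strongest reply is that this is a single clause, in a section about hiring and training advisors. The analysis section is neutral and speaks only of comparisons over time and across cases. The evaluation is a multiple case study with the workplace as unit. Its major outcomes are workplace-level changes in policy, procedures and practices, whereas the clause concerns individual workers' awareness and knowledge. The Summary names the design, defends it as realistic for workplaces, and mainly promises an understanding of how implementation proceeds. All of this stands. It keeps the point small and rules out any complaint that the design was hidden or should be replaced. It does not make the clause true.

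A reader might infer more than the documents support:

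- *That this difference will go to regulators as the program's effect.* The Phase 2 section promises briefing notes on particular outcomes and speaks of learnings about effectiveness. It ties neither to the two-wave worker survey.
- *That the plan fixes the raw difference as its estimator.* It gives no estimator, and a condensed article may leave that to a fuller document. No analysis method, however, would replace the missing comparator in this contrast.
- *That the bias can be expressed in percentage points or standard errors.* The number of workers surveyed, the clustering, the baseline level and the background shift are all unstated. Any such figure would rest on invented inputs.
- *That survey items on behaviors the program does not target, such as hearing or hand protection, would repair the contrast.* They would not respond to a hot summer or to sun-specific campaigns, so subtracting them would leave those influences in place.
- *That the contact list could supply a control.* The article says "Other potential participants were selected using a database of approximately 10,000 OHS professionals", so a list exists. A policy checklist sent to it would give no reference for worker survey answers, and the list is also a recruitment source and the dissemination channel.

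**Conclusion.** The causal wording is wrong as written. The baseline-to-second-wave survey difference identifies total change over the first summer, not the part caused by the program. This rests on features that the article states: no control, waves on either side of a summer, and program staff collecting both waves. It needs no assumption about how large the other influences are. Their size and net direction cannot be derived from the documents, and it remains possible that the program accounts for most of the change.

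The correction is at the level of wording, applied to one conclusion. It does not put in question the choice of an uncontrolled design, the case-study evaluation or the workplace-level outcomes.

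**What to change.** Reword the sentence under Recruitment of Sun Safety Advisors so that the comparison yields *change in workers' awareness, knowledge and practices over the program period*. Add that attribution to the intervention is limited by the absence of a control. Name the alternative explanations: season, secular trend, repeat surveying, and responses collected by the advisors who deliver the program. Use the same wording when the survey results are reported.

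This requires no new data, sites or analyses. The cost is a weaker claim: the surveys will describe change that accompanied the program, without saying how much of it the program caused.

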#### The Sun Safety at Work implementation

The Sun Safety Advisors will help the companies develop their programs and policies (Sun Safety Action Plans), based upon the findings of the base-line surveys and interviews. The action plan will be tailored to suit each workplace and will be embedded within the companies’ occupational health and safety risk assessment and control framework and risk management systems. It will describe the evaluation process of the project and will specify proposed sun safety activities, the timeline for implementation, who is responsible, and how these activities fit into the legal obligation to create a safe workplace. The action plan will be for 3 years and will extend beyond the project’s funding and direct involvement to ensure sustainability of the initiatives in the workplaces.

The action plan will take into account the financial and organization capacity of the workplace to implement the activities, and depending upon where a workplace is on their sun safety “journey,” will include a phased approach to the implementation of the selected activities. The ability of the workplace to sustain their sun safety program (after the study is over) and their overall stated level of change commitment and sense of efficacy will be a key determinant for the selection of activities and the development of the action plan.

During the first summer, the Sun Safety Advisors will lead the educational initiatives by delivering toolbox talks, showing videos, attending and contributing to joint occupational health and safety committees, giving health and safety meeting presentations regarding sun safety topics, promoting and exhibiting sun safe behavior including the wearing of appropriate PPE, and generally providing current and accurate educational advice to be disseminated to the workforce. They will also advise on how best to implement programs and sun safety change initiatives the employer chooses to undertake and help implement any of the initiatives from a suite of resources proposed by the study.

The suite of resources on different possible interventions has been developed as a group project of the full project coordinating team and the Sun Safety Advisors and the project’s knowledge broker. These materials were selected according to an evidence-based criteria and are based on a comprehensive review of all publically available sun safety resources nationally and internationally and particularly build upon materials developed by the Alberta-based *Be Sunsible* toolkit which identified a five-step process for implementing an effective sun safety program, plus the learnings from an Australian project, the QUT Outdoor Workers Project, which identified an eight-step process for implementing sun safety programs.

The resources include information on policy controls, engineering controls, administrative controls, personal protective equipment, and education and awareness strategies (including personal skin examination strategies). Policy interventions could include the development of a sun safe policy and long-term implementation plan for the workplace. Educational interventions include resources and education about skin cancer and heat stress. Screening interventions include encouraging skin self-examination. One change that has taken place since the original proposal is that the team has decided that organizing individual screening by a dermatologist or medical professional will be too onerous for most workplaces, and it has been dropped as a possible intervention.

To support the workplaces, the plan is to have a project website that will provide a portal for knowledge sharing and access to information and resources. This may include a weekly blog on sun safety topics of interest to the participants and a discussion board for interaction between the workplace champions, employees, and the project team.

